### Aims and Objectives

The BOOST DRG study is a randomized, controlled trial comparing the efficacy of SCS vs. DRGS vs. combination of SCS+DRGS (DUAL) and TCS vs. burst in a crossover design in patients with chronic lower limb neuropathic pain and/or neuropathic back pain.

The primary objective of this study is to compare the efficacy of SCS vs. DRGS vs. DUAL on global pain relief in patients with chronic lower limb neuropathic pain and/or neuropathic back pain.

Secondary objectives are to compare pain intensity, pain surface and paresthesia coverage surface to assess positional or postural effects on paresthesia, to compare changes in quality of life, functional disability and psychological state, to assess patient satisfaction and, finally, to compare the effects of stimulation modalities on brain imaging based on fMRI and EEG. Using this study data, we will extract baseline factors associated with long-term stimulation efficacy. These predictors will be included in a predictive model.

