### 2.1. Design and Setting

The BOOST DRG study is divided into two phases.

Phase A (Pilot study) is a randomized, double-blinded, crossover, six-arm study evaluating the feasibility and comparing the efficacy of three stimulation modalities: SCS, DRGS and DUAL (SCS+DRGS) on 12 patients during 3-month follow-up, which will be conducted only in Poitiers University Hospital (France). According to the phase A results, in terms of feasibility and safety, a second phase is planned, following the same design and including a larger sample of patients, internationally, to take into account the variability of practices.

Phase B (Main study) is a prospective, multicentric, randomized, double-blinded, crossover, six-arm study comparing the efficacy of three stimulation modalities: SCS, DRGS and DUAL stimulation (SCS+DRGS) on 54 patients, conducted in the Poitiers University Hospital (France), the Colmar Louis Pasteur Hospital (France) and in Genève Tower Hospital Pain Clinic/Lausanne University Hospital (Switzerland).

Phase A and phase B have the same design. Patients will be implanted with the Octrode^TM^ contact percutaneous lead for SCS and one or several Quattrode^TM^ lead(s) for the DRGS, enabling use of the three different stimulation modalities in the same patient. The leads will be connected to a single external pulse generator. Patients will be randomized in 6 different arms in a 1:1:1:1:1:1 ratio: SCS alone, DRGS alone and DUAL stimulation. During the 3-month crossover period, patients will be under the tonic conventional stimulation (TCS) waveform, whatever the stimulation modality. Each stimulation modality will be administered for 1 month. Patients will be assessed at the end of each stimulation modality period, corresponding to the 1-month, 2-month and 3-month follow-up visits. At the end of the crossover period, stimulation modality will not be changed and will be switched to the burst waveform for 1 month. Patients will be assessed at the end of this 1-month period, corresponding to the study’s 4-month follow-up visit. Patients will then decide which stimulation modality and waveform they prefer and will be assessed at 6 months and 12 months.

Patient flow and the study design are presented in Table 1 and Figure 1, respectively.

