### 2.6. Procedures to Minimize Bias

To minimize selection bias, the randomization list will be prepared using the random selection program Ennov Clinical. Randomization numbers will be assigned in strict sequence; when a subject is confirmed as eligible for randomization, the next unassigned randomization number in sequence will be given. Randomization allocation will be concealed from the evaluator and subject, using a centralized automatic web-based data management system dedicated to the study and accessible to investigators by username and personal password (CS Online 7.5.10.11). Once assigned, the randomization assignment for the subject cannot be changed. Early departure from the study does not give rise to placement or reassignment of the rank of inclusion.

Due to the paresthesia generated by the TCS waveform, during the crossover period, patients will be under TCS waveform, whatever the type of stimulation. Consequently, patients will not be able to distinguish if they are under DRGS, SCS or DUAL stimulation. At the 3-month follow-up visit, all the patients will be switched to the burst waveform for a 1-month period while keeping the last allocated stimulation type in the randomized crossover arm. Patients will keep their stimulation in order to achieve optimal comparability between TCS and burst parameters.

To allow for investigator blinding, the evaluator will be different from the person who programs the IPG.

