Continuous outcomes at 4-month of burst DRGS, burst SCS and burst DUAL stimulations will be compared using an ANOVA or a Kruskal–Wallis test. In case the ANOVA (or Kruskal–Wallis test) is significant, a pairwise comparison will then be conducted using independent *t*-test or Mann–Whitney test depending on the variable distribution. A Holm–Bonferroni correction will be applied on the pairwise comparison.

The categorical outcomes will be compared using a Chi-squared test or an exact Fisher test when the Chi-squared assumptions are not met. A generalized mixed-effects model with a patient specific random intercept will be used to estimate the global treatment effect including the 6-month and 12-month follow-ups. The link function used in the model will depend on the type of the studied outcome (logistic or multinomial for categorical outcomes and no link function for continuous outcome).

The relationship between performance (percentage of pain covered with stimulation) and “induced” pain relief (global pain VAS) will be estimated by Kendall’s tau and its 95% confidence interval. The correlation between selectivity (percentage of paresthesia covering pain) and paresthesia discomfort will also be estimated using Kendall’s tau.

Mean energy consumption will be compared between the different types of stimulation using repeated measures ANOVA or a Friedman test.

Tonic stimulation will be compared to burst stimulation using patient last crossover stimulation modality. The comparison will be conducted using a paired *t*-test or a Wilcoxon signed-rank test using data from the last crossover period compared to the 4-month data using burst stimulation. VAS decrease will be compared between all the SCS modalities at 6-month and 12-month follow-ups using a two-factor ANOVA (preferred anatomical target x preferred stimulation type).

A sub-analysis of the sample will be conducted in order to assess the effect of burst waveform on the brain signals visualized using brain imaging data with and without burst stimulation.

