### 3.5. Study Limitations

Despite potential interest, this study has several limitations. First, as mentioned above, the comparison between TCS (involving a paresthetic effect) versus burst (a paresthesia-free modality) will not be performed under strict and homogeneous blinded conditions, by sequentially testing the different stimulation modalities. However, burst will be applied for the three groups (SCS, DGRS and DUAL) between the 3rd and the 4th month after randomization, which will allow for the comparison of paresthesia-free conditions as a second step, in a second phase. This should not interfere with our main endpoint, at 3-month follow-up, involving TCS and paresthesia for each group of stimulation, in a strict double-blind manner. Second, this crossover design will not allow us to determine long-term efficacy of each stimulation modality, since multiplying the number of modalities to evaluate implies proportionally decreasing the length of the follow-up period for financial and ethical reasons. An alternative point of view would counterbalance this loss of potential valuable information with the fact that this design can also be considered as “added value” for the patient, who will be able to choose his preferred spatial target and waveform, thereby enhancing treatment adherence. Following this perspective, we will collect maximal follow-up for the stimulation modality, which will reflect the patient’s preference. Third, the absence of wash-out period will not allow us to claim that one modality could not induce a carryover effect. However, the 1-month period used for each modality should cancel out this potential carryover effect. Fourth, mechanisms of actions will be assessed at the supraspinal level, even though some modulations can occur at the spinal level. In their in vitro simulation study, Zannou et al. [74,75] interestingly reported tissue heating when stimulation was applied at a high-frequency modality, which that may impact more or less long-term clinical outcomes. Realistic anatomical computational models of SCS are crucial tools and provide opportunities to better understand the role of complex tissue compartments in shunting the current applied to the potential neural targets [74,75,76].

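### Secondary analyses treat patient-chosen months 6 and 12, and a fixed-order tonic-to-burst switch, as treatment comparisons although neither is randomised

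*Protocol article*

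**What the plan says.** Section 2.1 randomises one thing: the order of SCS, DRGS and DUAL over months 1–3, all under tonic stimulation. Section 2.6 fixes month 4 for everyone: "all the patients will be switched to the burst waveform for a 1-month period while keeping the last allocated stimulation type". After that, section 2.1 states: "Patients will then decide which stimulation modality and waveform they prefer and will be assessed at 6 months and 12 months".

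Section 2.7.2 then plans three analyses that reach beyond the randomised contrasts:

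- A generalized mixed model with a patient-specific random intercept, which "will be used to estimate the global treatment effect including the 6-month and 12-month follow-ups".
- A comparison of VAS decrease at months 6 and 12 by a "two-factor ANOVA (preferred anatomical target x preferred stimulation type").
- A paired t-test or Wilcoxon signed-rank test of tonic against burst, "using data from the last crossover period compared to the 4-month data using burst stimulation".

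The Aims and Objectives describe the waveform question as "and TCS vs. burst in a crossover design". Section 3.5 says that "this crossover design will not allow us to determine long-term efficacy of each stimulation modality".

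**The concern.** Groups defined by preference at months 6 and 12 are formed after patients have experienced each modality, so membership can depend on the outcome being compared. A random intercept absorbs a patient's general level of relief. It does not absorb the fact that a patient who does unusually well on DRGS is more likely to be observed on DRGS later. The protocol expects such differences: section 3.1 allows for patients who would fail one technique but not the other, and seeks responder characteristics by target.

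The waveform comparison has a different fault. It is within patient, so patient characteristics are balanced. But waveform and calendar position coincide exactly, and any drift, carryover or expectation effect between months 3 and 4 is credited to burst.

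At stake is a set of p-values for modality and waveform that look like treatment effects but are not protected by randomisation.

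**Working it through.** **Which contrasts are randomised**

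| Contrast | Basis | Randomised? |
|---|---|---|
| SCS, DRGS, DUAL under tonic, months 1–3 | allocated order | yes |
| SCS, DRGS, DUAL under burst, month 4 | last allocated modality | yes |
| Tonic vs burst, month 3 vs month 4 | same order for all | no |
| Modality and waveform, months 6 and 12 | patient's choice | no |

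The last two rows carry hypothesis tests in section 2.7.2 with no observational label. That section does label the second interim analysis as purely descriptive, so the distinction was available. It also places all analyses under the intention-to-treat principle, which gives no protection to groups defined by a later choice.

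**Size of the selection effect (illustration)**

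The documents give no variance components or choice rule, so these inputs are assumed: relief in points of percentage VAS decrease, between-patient SD 15, residual SD σ = 15, and choice of the modality with the best observed crossover result. Let τ be the patient-by-modality SD.

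With equal true means and equal τ, the rise in the later mean is 0.846 × τ² / √(τ² + σ²), where 0.846 is the expected maximum of three standard normals. For τ = 15: 0.846 × 225 / 21.21 = 9.0, so 55 becomes 64.

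Simulation gives these month-6 means by chosen modality (SCS / DRGS / DUAL), with true means all 55:

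| Patient-by-modality SDs | Month-6 means | Spurious contrast |
|---|---|---|
| 0 / 0 / 0 | 55 / 55 / 55 | none |
| 15 / 15 / 15 | 64 / 64 / 64 | none, but all means up 9 |
| 14 / 17 / 14 | 63 / 66 / 63 | about 3 |
| 10 / 25 / 10 | 59 / 74 / 59 | about 15 |

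With a true DRGS advantage of 15 points and all SDs 15, the by-choice difference is about 10. In the pooled mixed model the randomised months dilute the bias: under the 10/25/10 case the spurious effect is about 3 to 4 points.

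**Size of the fixed-order effect (illustration)**

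Assume no burst effect and a within-patient residual SD of 20. The SD of the paired difference is 20 × √2 = 28.3. For drift d and n patients, the noncentrality is d / (28.3 / √n). At d = 5 this is 1.22 for n = 48 and 1.44 for n = 66. Two-sided rejection at the 0.05 level, from the noncentral t distribution:

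| Drift | n = 48 | n = 66 |
|---|---|---|
| 2.5 | 9% | 11% |
| 5 | 22% | 29% |
| 10 | 67% | 81% |

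**The case against.** The article is partly open about both limits. Section 3.1 says its comparative design does not carry over to the comparison of waveforms. Section 3.5 says that this comparison is not strictly blinded and that there is no washout. The ANOVA factors are themselves named as preferences, so no reader would take those groups for randomised ones. The mixed model's fixed effects are not listed, and time or choice terms may appear in a fuller document.

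Most of this stands as mitigation, not as an answer. Section 3.5 attributes the long-term limit to short periods and never names self-selection; neither section names fixed order or drift. No added fixed effect can make chosen-modality data randomised, or separate waveform from time when the two coincide.

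Some stronger readings are tempting but unsupported:

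- A reader might infer that a spurious 15-point modality difference is to be expected. It appears only under strongly unequal patient-by-modality SDs, for which the documents offer no basis.
- A reader might infer that patients pick whatever relieved pain best. The protocol speaks of preference, which may also reflect comfort or paresthesia. Choosing the best observed modality is a modelling assumption.
- A reader might infer that the primary result or the month-4 burst comparison is compromised. Both use randomised allocation.

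**Conclusion.** The concern holds for secondary analyses only. The month-6 and month-12 model and ANOVA compare self-selected groups, and the paired tonic–burst test measures a change after a switch, not a waveform effect. The aims wording and the global-effect wording claim more than sections 3.1 and 3.5 allow.

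The size cannot be derived from the documents. Under the stated assumptions the modality bias runs from nil, when patients do not differ in response by modality, through inflated means with no spurious contrast, to about 15 points in an extreme case. True differences can also be attenuated. The rejection rates for the paired test rest on an assumed residual SD of 20 and an assumed drift; the documents do not say that drift will occur. This should be corrected before analysis, but it does not threaten the primary conclusion.

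**What to change.** - Restrict the model for modality effects to randomised data: months 1–3 within patient, and month 4 between the groups defined by randomised last modality.
- Report months 6 and 12 by chosen modality as descriptive or observational, with each patient's change from their own crossover value and without confirmatory p-values. The two-factor table can stay if it carries that label.
- In the Aims and Objectives, drop the crossover description for tonic versus burst. Report month 3 to month 4 as an uncontrolled before-after change.
- Period estimates from months 1–3 may be shown beside it as context. They should not be used as a correction, because that would assume the same trend continues into month 4.
- In section 3.5, name self-selection and fixed order as sources of bias.

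The cost is wording in the aims, analysis and limitations sections. No visit, patient or procedure changes. The sponsor gives up inferential claims for the self-selected long-term groups and for the tonic–burst switch.

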#### 2.2.3. Exclusion Criteria

The patient is unable to appropriately use stimulation equipment, the patient has failure of the trial phase, defined as pain reduction <50% between the inclusion visit and 7 days after lead implantation or the patient presents with any medical condition judged as relevant/significant by the investigator.

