Potential lead migration should be documented by imaging in case the patient experiences inadequate pain relief and/or for coverage after initial positive outcome. In case of lead displacement, documented by X-ray, a revision surgery will be recommended to check hardware dysfunction, including lead migration or fracture. This complication will be reported as an adverse event. Pain rating and outcomes will be analyzed taking the adverse event into account.

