Two interim analyses are planned. The first interim analysis will be conducted on data from the first 12 patients included (after the “Tonic” crossover period). In this first interim analysis, we will analyze only the safety criteria, the objective being to assess study feasibility. The second interim analysis will be conducted on data from the first 33 patients included (after the “Tonic” crossover period) and will be exclusively descriptive. No hypothesis testing will be conducted. This analysis will be conducted on primary and secondary outcomes. As the study is of long duration (3.5 years), we decided to include a second interim analysis to communicate the results to the scientific community by clearly indicating that this is an interim analysis and that the final analysis will be conducted on the total sample of 66 patients. This may lead to other projects and accelerate the progress of research on the stimulation of several anatomical targets. These results will have no impact on study completion. The final analysis on 66 patients will be considered for the report and the publications.

Only data from the crossover period will be used in the interim analysis. The statistical methods used in this interim analysis will be similar to the methods used in final analysis described above. No adjustment of the final analysis *p*-values will be conducted as the interim analysis results do not influence in any way the course or the conduct of the study.

A significance level of 0.05 will be considered in this study (after taking into account multiple testing corrections) and all tests will be two-sided.

All the analyses will be conducted based on an Intention-To-Treat (ITT) principle using complete cases. No missing data imputation will be conducted. An initial safety analysis will be conducted on the first 12 patients to assess the initial safety of implementing patients with both DRG and SCS stimulations. A final safety analysis will be conducted on the 66 patients. Frequencies of adverse events and deviations from protocol will be compared between the treatments following an ITT analysis.

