**Figure 2 medicina-58-00007-f002:**
[figure not shown]
An artistic view illustrating SCS and DRGS implantation.

**Table 1 medicina-58-00007-t001:** Radio-clinical assessment calendar.

	Inclusion Visit	Implantation Visit (Within 2 Months after Inclusion)		Visit M1 [1 Month ± 1 Week /M0]	Visit M2 [1 Month ± 1 Week /M1]	Visit M3 [1 Month ± 1 Week /M2]	Visit M4 [1 Month ± 1 Week /M3]	Visit M6 [2 Months ± 2 Weeks /M4]	VisitM12 [6 Months ± 3 Weeks /M6]
		Lead Implantation Visit	Visit M0 (IPG Implantation + Randomization)						
Patient information and consent form (R)	✓								
Inclusion and non-inclusion criteria (R)	✓								
Exclusion criteria (R)									
Socio-demographic data (C)	✓								
Medical and surgical history (C)	✓								
Spine MRI + thoraco-lumbar X-rays (front + profile) ^1^ (C)	✓								
painDETECT Questionnaire (C)	✓								
Brain imaging (fMRI/EEG) ^2^ (R)	✓ ^3^					✓	✓		
VAS (C) *	✓								
ODI(C) *, HADS(C) *, PCS(R) *, EQ5D-5L(C) *	✓			✓	✓	✓	✓	✓	✓
Spine X-ray (C)		✓(post-impl)							
Mapping of the painful territory (C) *	✓	✓	✓(post-impl)	✓	✓	✓	✓	✓	✓
Mapping of paresthesia coverage (C) *		✓(post-impl)	✓(post-impl)	✓	✓	✓	✓	✓	✓
Stimulation parameters and programming (C)		✓(post-impl)	✓(post-impl)	✓	✓	✓	✓	✓	✓
Patient satisfaction (PGIC) (C) *			✓(post-impl)	✓	✓	✓	✓	✓	✓
Paresthesia discomfort 11-point NRS (C) *				✓	✓	✓	✓	✓	✓
5-day VAS diary (R)									
Concomitant medications ^3^ (C)									
AE/SAE/Device deficiencies									

^1^ Only if not already available, dating >2 years or since the last spinal surgery; ^2^ Only for patients from Poitiers University Hospital; ^3^ To schedule between inclusion and lead implantation visit; * to perform through a touchscreen tablet; (R): specific to the research; (C): as per standard care. The arrow indicates exclusion criteria was performed in every visit.

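### The plan calls its analyses ITT but runs them on complete cases, and does not say how data are handled when a randomised patient meets an exclusion criterion after M0

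*Protocol article*

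**What the plan says.** Section 2.7.2 sets one rule for everything: "All the analyses will be conducted based on an Intention-To-Treat (ITT) principle using complete cases". It adds: "No missing data imputation will be conducted". The same section promises that "the final analysis will be conducted on the total sample of 66 patients". Section 2.7.1 expects 17% dropout, made up of losses to follow-up and possible explants, and Section 2.6 provides no replacement for patients who leave early.

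The primary endpoint is binary (a 50% reduction in global VAS) and is measured in each of three one-month periods. Section 2.7.2 starts with a mixed-effects logistic model with a random subject intercept. If the period effect is not significant, it moves to Cochran's Q followed by pairwise McNemar tests. Continuous secondary outcomes use repeated-measures ANOVA.

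Randomisation takes place at IPG implantation, M0 (Section 2.5 and Table 1). The Table 1 note says: "The arrow indicates exclusion criteria was performed in every visit". Section 2.2.3 lists three exclusion criteria:
- "The patient is unable to appropriately use stimulation equipment"
- "failure of the trial phase, defined as pain reduction <50% between the inclusion visit and 7 days after lead implantation"
- "the patient presents with any medical condition judged as relevant/significant by the investigator"

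For displaced leads, Section 2.3.1 says: "Pain rating and outcomes will be analyzed taking the adverse event into account".

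**The concern.** ITT keeps every randomised patient, whereas a complete-case analysis keeps only those with the required data. Section 2.7.2 promises both, and also promises 66 patients. The label therefore does not tell a reader who is in the primary analysis.

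The order of visits adds to this. Exclusion checks continue after M0, one criterion is left to the investigator's judgement, and nothing states whether the data of a randomised patient who meets a criterion stay in the analysis. The sentence on displaced leads keeps those outcomes in but does not say how the adverse event enters the analysis.

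What is at stake is the three-way comparison of response rates. With a binary endpoint, whether a lost period is dropped or counted as a failure changes the rate directly. If patients leave because a modality failed them, dropping their periods flatters that modality. Deleting whole patients also discards valid observations from the periods they completed.

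**Working it through.** **Inputs.** From Section 2.7.1: 48 patients required, 66 planned, 17% dropout, response 81.2% on DRGS (56/69) and 55.7% on SCS (39/70). No DUAL rate is given. From Section 2.7.2: three periods per patient, the mixed model, Cochran's Q and McNemar.

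**The plan's own figures.** The 48 cannot be settled from what is stated, because neither the within-patient correlation nor a DUAL rate is given. A two-sided McNemar calculation at 90% power for DRGS against SCS gives 71 patients with no correlation, 49 at 0.35 and 46 at 0.40. Inflating for dropout, 48 / 0.83 = 57.8, so 58. The plan goes to 66 and also cites its secondary objectives.

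**Expected complete cases.** 66 × 0.17 = 11.2, so about 11 losses and about 55 complete patients (66 × 0.83 = 54.8). That is not 66, but it still exceeds 48.

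**What each method loses.** Assume 11 patients each miss one crossover period. Observed periods are 66 × 3 − 11 = 187.
- Cochran's Q, and classical repeated-measures ANOVA, need all three periods. They use 55 patients and discard 11 × 2 = 22 observed periods (22 / 187 = 12%).
- McNemar needs two periods. A patient missing one period leaves two of the three pairs and stays in the third. With losses of 4, 4 and 3 under SCS, DRGS and DUAL, the pairs keep 66 − 8 = 58 (SCS, DRGS), 66 − 7 = 59 (SCS, DUAL) and 66 − 7 = 59 (DRGS, DUAL).
- The mixed model uses all 187 periods if complete cases means per record. It uses 55 × 3 = 165 if it means per patient.

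**Which exclusions can act after randomisation.** Inability to use the equipment and the investigator-judged condition can both arise after M0. The 50% criterion is fixed at 7 days after lead implantation, and passing the trial phase is a condition for IPG implantation (Sections 2.3.2 and 2.3.3), so it acts before randomisation. The explant exclusion in Section 2.3.2 belongs to the paragraph on trial failure and also acts before randomisation.

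**Illustration of sensitivity.** Assume the 11 missing periods all fall in the crossover and that response among observed periods stays at 81.2% and 55.7%. Complete cases give 81.2 − 55.7 = 25.5 points. Counting a missing period as non-response multiplies a modality's rate by (66 − m) / 66, where m is its number of missing periods:

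| Missing periods (SCS/DRGS/DUAL) | SCS | DRGS | DRGS − SCS |
|---|---|---|---|
| 0/11/0 | 55.7% | 81.2 × 55/66 = 67.7% | 12.0 |
| 11/0/0 | 55.7 × 55/66 = 46.4% | 81.2% | 34.8 |
| 4/4/3 | 55.7 × 62/66 = 52.3% | 81.2 × 62/66 = 76.3% | 24.0 |

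**The case against.** A reader might infer that the plan removes randomised patients for inefficacy or device failure. The documents do not support this. The inefficacy criterion and the explant rule act before randomisation. After implantation, Sections 2.3.1 and 2.3.3 answer displacement or inadequate relief with imaging, reprogramming or possible surgery, and Section 2.3.1 says the outcomes are analysed. The fault there is only that the adjustment is undefined, and its detail may sit in the full protocol or SAP.

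A reader might also infer that DRGS response will be inflated. That cannot be shown. No section says which modality loses more hardware. DUAL uses the same DRG leads, so failures confined to DRGS periods are implausible. The 17% is applied to patients included, inclusion precedes the lead trial, and follow-up runs to 12 months, so 11 losses within the crossover is an assumption.

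The mixed model can already keep a dropout's completed periods, and about 55 complete cases exceed the 48 required. Both points stand: patients need not be lost on that route, and the problem is not one of numbers.

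Finally, counting device-related gaps as non-response is a choice of estimand and a form of imputation. That also stands, and it is a reason to make it a sensitivity analysis.

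None of this resolves the conflict between ITT, complete cases and 66 patients, or supplies a rule for data after a post-M0 exclusion.

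**Conclusion.** The point holds in a limited form. The analysis set is contradictory as written: ITT, complete cases without imputation and a final analysis on 66 cannot all apply when about 11 losses are expected. The meaning of complete cases is open for the mixed model and amounts to whole-patient deletion for Cochran's Q and repeated-measures ANOVA. Two of the three exclusion criteria can act after randomisation with no stated rule for the data.

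The effect on the DRGS–SCS difference is undetermined. The illustrative range of about 12 to 35 points around 25.5 rests on three assumptions: all 11 losses fall in the crossover, each costs one period, and observed response equals the cited rates. The ends of the range put every loss under one modality; an even spread moves the difference by only 1.5 points (25.5 − 24.0). The range shows that the result could depend on the handling of losses; it does not predict a bias.

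**What to change.** 1. Define the primary analysis set as all randomised patients and keep every observed patient-period in the mixed logistic model. No imputation is needed, but validity then rests on the missing periods being missing at random, which is why item 4 is needed.
2. State that data from patients who meet an exclusion criterion after M0 are retained in the analysis.
3. State that outcomes after lead migration stay in the primary analysis as randomised, with any adjustment for the adverse event as a sensitivity analysis.
4. Report complete cases as a sensitivity analysis; Cochran's Q belongs there because it needs all three periods. Add one that counts periods missing because of explant, lead failure, or withdrawal for lack of effect or adverse event as non-response.

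The cost is revised wording in Sections 2.7.2 and 2.3.1 and the Table 1 note, a little more analysis work, and possibly less favourable response rates. No extra patients or visits are required.
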